#### Secondary outcomes

Patient-reported outcome measures to assess secondary outcomes relevant to the clinical effectiveness evaluation are described. A feasibility study was not conducted prior to the RCT; therefore, feasibility and implementation data will be collected.

*Ida Institute Readiness to Take Action (Line 1)*,^39^ visual analogue scale, 0–10.*Ida Institute Self-efficacy to Take Action (Line 2)*,^39^ visual analogue scale, 0–10.*Revised Hearing Handicap Inventory-Screening*,^40^ validated, 10 items, 3-point Likert Scale (yes, sometimes, no).*Empowerment Audiology Questionnaire*,^41^ validated, 5 items, 5-point Likert Scale (strongly disagree to strongly agree, not applicable).*WHO Health and Work Performance Questionnaire*,^42^ validated, adaptive subset of questions on paid/unpaid work.*Intention to take action*, 11 healthcare options, contact HCP, family doctor or hearing support organisations. This question will also be delivered at the 1m email reminder.*Preparedness for Decision-making*, validated,^43^ 10 items, 5-point Likert scale (not at all to a great deal).*User-Mobile Application Rating Scale*,^44^ validated, subset of 6 items for perceived impact, 5-point Likert scale (strongly disagree to strongly agree).*Action taken*, 11 healthcare options, contact HCP, family doctor or hearing support organisations. This question will also be delivered at the 1m email reminder.*Glasgow Hearing Aid Benefit Profile*,^45^ validated, four items (use, benefit, residual disability, satisfaction) across four pre-defined situations, 5-point response specific to the situation and item (0=100%). Only for those who take up hearing aids.*Feasibility* (acceptability, usability, usefulness, satisfaction, accessiblity), 10 items, 5-point Likert scale (not very much to very much so).*Consent rate*, completion of outcomes at T0 compared with those who are eligible (%).*Attrition rate*, completion of outcomes at T1 compared with T0 (%).*Adoption*, uptake of intervention (*HearChoice*, Option Grid) across the study.*Fidelity*, time spent adhering to the allocated intervention across the study (s).

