## Introduction

### Background and rationale

 One in seven Australian adults has hearing loss (approximately 3.95 million), which is estimated to increase to 7.78 million by 2066.^1^ The negative impacts of hearing loss are pervasive, impacting communication, interaction with others and social engagement, leading to overall poorer health and well-being,^2^ as well as reduced employment, income, advancement and well-being in the workplace.^3^ Additionally, hearing loss in midlife is a primary potentially modifiable risk factor for dementia.^4^ Despite hearing aids being clinically effective,^5^ only one in three people who would benefit from hearing aids have them.^6 7^ There is a significant time delay of 8.9 years, on average, from becoming aware of hearing difficulties to obtaining hearing aids.^8^ Additionally, the majority of working-aged adults aged between 26 and 64 years, and many who are retired, are not eligible for fully or partially subsidised hearing healthcare through the Australian Hearing Services Programme (HSP). These barriers and low uptake of hearing healthcare contribute to the economic cost of untreated hearing loss to the Australian economy reported at $A 41 billion in 2019–2020.^1^

Low uptake of hearing healthcare is common, with many people not seeking help for hearing problems.^9^ This issue was highlighted by the HSP review published in 2021 that found 60% of those eligible for the HSP do not engage with it.^10^ Understanding the reasons for low uptake of hearing healthcare early in the hearing journey is important to reduce the burden of untreated hearing loss in Australia. The HSP review reported barriers including poor understanding of the impacts of hearing loss, inappropriate expectations about hearing aids, and a lack of information, or misinformation, about hearing loss, hearing aids and other rehabilitation options. For example, a large proportion of people do not believe hearing aids provide benefits.^10^

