### Participants

#### Eligibility criteria

The inclusion criteria are: (1) aged 26 years and older, (2) subjective experience of hearing difficulty, (3) currently residing in Australia, (4) regular access to a computer, tablet or smartphone to navigate websites and (5) a good understanding of English. The exclusion criterion is current users of hearing aid(s).

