#### Sample size

We aim to recruit a sample of 640 participants at randomisation. This sample size is based on a required sample of 352 at T1 and a rate of 45% attrition between T0 and T1. This rate of attrition is typical for studies completed using the Predictiv platform.

The required sample size at T1 was calculated as necessary to detect a moderate effect size of 0.3 at 80% power and an alpha level of 0.05 in a two-tailed test. This moderate effect size was selected pragmatically as there are no published RCTs of decision aids for hearing interventions. Review of previous RCTs of patient decision aids for other, mainly chronic, conditions using the Decisional Conflict Scale revealed a wide range of reported effect sizes (0.03–3.94).^32 33^ The selected effect size of 0.3 is slightly smaller than that reported in a previous study of a similar online decision aid.^34^

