	**Effectiveness outcomes**			
Primary outcome				
Decisional conflict	Decisional conflict Scale	X	X	X
Secondary outcomes				
Readiness for hearing healthcare	Ida Institute Line 1	X	X	X
Self-efficacy for hearing healthcare	Ida Institute Line 2	X	X	X
Hearing-related quality of life	Revised Hearing Handicap Inventory—Screening	X		X
Empowerment	Empowerment Audiology Questionnaire—15 items	X	X	X
Intention to take action	Bespoke project-related question		X	X
Preparedness for decision-making	Preparation for Decision-making Scale		X	X
Impact of the decision tool	User-Mobile Application Scale—User		X	X
Action taken	Bespoke project-related question		X	X
Benefit of hearing aids	Glasgow Hearing Aid Benefit Profile Part 2			X
Economic benefit	WHO Health and Work Performance Questionnaire	X		X

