#### Statistical methods

A full statistical analysis plan will be finalised prior to data lock. No interim analyses to stop for efficacy or futility are planned.

Demographic and hearing characteristics of the intervention and control groups will be described at T0. For the primary and secondary outcome measures at each timepoint (T0, T1, T2), we will provide the mean and 95% CIs by group. Differences between groups will be explored at each timepoint using independent samples t-tests, with correction for Type I errors as required. The primary analysis will evaluate whether there is a difference between the intervention and control groups at the primary study endpoint T1.

Analysis of variance will be used to compare change over time on each outcome measure between the intervention and control groups. Additional analyses will be performed to explore the impact of demographic, hearing-related characteristics and intervention engagement on the outcome measures over time between groups.

Economic analysis involves estimation of societal costs and costs associated with the development and use of the decision aid, and costs of fitting hearing aids or equivalent. Additionally, the impact of the intervention of work will be explored on both employment status (focusing on hours of work per week), and measures of absenteeism and presenteeism, specifically the WHO Health and Performance Questionnaire.^42^

Acceptability and feasibility data will be summarised by descriptive statistics and compared within and between intervention groups. This will include a flow diagram of the numbers of participants across the trial as indicated in figure 1 (eg, number screened, eligible, completion at each timepoint). For the *HearChoice* group, additional analyses using website analytics on participants’ engagement with *HearChoice* across the trial period will be performed based on content viewed. These results, along with those from the evaluation outcome measures, will help inform future trials of decision aids in hearing healthcare.

After completion of all planned analyses, data will be made available on reasonable request and on signing a unilateral data sharing agreement.

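### Hearing-aid benefit is measured only in participants who take up aids after randomisation, yet it falls under the between-group t-tests, so that comparison is not a randomised one

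*Protocol article*

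**What the plan says.** All references are to the protocol article.

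- **Status of the outcome.** Table 1 lists "Glasgow Hearing Aid Benefit Profile Part 2" among the secondary effectiveness outcomes, with a mark at T2 only.
- **Who completes it.** The Secondary outcomes section restricts it: "Only for those who take up hearing aids".
- **Entry.** Eligibility criteria exclude people who currently use hearing aids. Sequence generation places randomisation at entry to T0.
- **Analysis.** Statistical methods states: "For the primary and secondary outcome measures at each timepoint (T0, T1, T2), we will provide the mean and 95% CIs by group". The next sentence reads: "Differences between groups will be explored at each timepoint using independent samples t-tests, with correction for Type I errors as required". It then adds: "Analysis of variance will be used to compare change over time on each outcome measure between the intervention and control groups". None of these sentences exempts the Glasgow Profile or gives it descriptive status.
- **What the arms see.** Under Interventions, HearChoice covers 11 options (five non-device, including doing nothing, and six technological). The Option Grid covers three: hearing aids, assistive listening devices and doing nothing. The Abstract gives uptake of hearing healthcare as one of the things HearChoice is meant to promote.

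**The concern.** Randomisation makes the two arms comparable as whole groups. It does not make comparable the subsets who later choose hearing aids, when that choice can depend on the arm. A wide menu may steer people with milder difficulty towards other options. A fuller decision aid may instead bring in more hesitant people. In either case adopters in the two arms could differ in severity or motivation, and mean benefit could then differ although neither intervention alters the benefit a given person gets from an aid. A real effect could equally be hidden. Recruiting more people would not remove this.

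At stake is a p-value under an effectiveness heading that readers would take as evidence on whether HearChoice improves hearing-aid benefit, when the design cannot supply that evidence.

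**Working it through.** **1. Reproducing the plan's own sample size.** The inputs from Sample size are a standardised difference of 0.3, 80% power and two-sided alpha of 0.05.
- Normal approximation: n per arm = 2 × (1.960 + 0.842)² / 0.3² = 174.4, so 175 per arm and 350 in all.
- Noncentral t: 176 per arm, 352 in all (power 80.1%). This matches the stated 352 at T1.
- Attrition of 45%: 352 / (1 − 0.45) = 640. This matches the number to be randomised.

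**2. Which planned analyses can apply.**

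| Planned analysis | Glasgow Profile |
|---|---|
| Mean and 95% CI by group | Possible at T2, among adopters only |
| t-test at each timepoint | Possible at T2, but between post-randomisation subsets |
| Analysis of variance of change | Not possible: no T0 or T1 value |

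**3. Size of the subset.** The article gives no uptake rate and no attrition figure for T2. Uptake is therefore an assumption, shown as a range. I take 352 responders at T2, meaning no further loss after T1, and equal arms. Power is from the noncentral t with noncentrality 0.3 × √(n/2), where n is the number per arm.

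| Assumed uptake | Adopters (352 × rate) | Per arm | Power for 0.3 | Difference detectable at 80% power |
|---|---|---|---|---|
| 3% | 10.6 | 5 | 7.0% | 2.02 SD |
| 5% | 17.6 | 9 | 9.2% | 1.41 SD |
| 10% | 35.2 | 18 | 14.1% | 0.96 SD |
| 20% | 70.4 | 35 | 23.6% | 0.68 SD |

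If all 640 were followed to T2, 3% to 20% uptake would give 19 to 128 adopters and power of about 10% to 39%. With 194 responders at T2 (55% of 352, also assumed), it would give about 6 to 39 adopters and power of about 6% to 15%.

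**4. Selection alone, as an illustration.** Suppose benefit is normal with SD 1, has correlation ρ with a latent propensity to take up aids, and is not affected by arm. If a fraction p takes up aids, mean benefit among adopters is ρ × φ(z) / p, where z is the upper p-quantile of the normal distribution and φ its density.
- p = 3%: φ(z)/p = 2.268.
- p = 6%: φ(z)/p = 1.985.
- The difference is 0.283. Multiplied by ρ = 0.3 it is 0.085 SD; by ρ = 0.5 it is 0.141 SD.
- With 5% v 10% the corresponding values are 0.092 and 0.154 SD.

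So with no effect on benefit, a doubling of uptake produces an expected difference of about 0.09 to 0.15 SD, with the lower mean in the arm with more adopters. The correlations and uptake rates are assumed. The calculation shows the mechanism and does not predict its size in this trial.

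**The case against.** The strongest reply is that the article is a summary. It says the t-tests will explore differences, and it promises a full analysis plan before data lock. Its blanket sentences cannot be meant literally for every listed outcome, since consent rate and attrition appear in the same list. By-group means with confidence intervals are also close to descriptive reporting. This lowers the weight of the point but does not answer it: the article states a method for the secondary outcomes, and that method is unsuitable for this one.

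Three stronger readings are tempting, and the article does not support them.

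- **That the comparison rests on a handful of people.** A reader might infer this from the Background statement: "There is a significant time delay of 8.9 years, on average, from becoming aware of hearing difficulties to obtaining hearing aids". Treated as a constant hazard, it gives 1 − exp(−0.25/8.9) = 2.8% over 3 months, or about 10 of 352. But it is an average over the whole period from first awareness. Participants enter at unknown points in that period, and both arms receive a decision aid and a 1-month reminder. At 10% to 20% uptake the subset would be 35 to 70 people.
- **That nobody enters with hearing aids.** Only current users are excluded. People who own unused aids or have stopped using them may enter and may resume.
- **That a randomised comparison of uptake is absent, or could be had complete in everyone.** *Action taken* is already a secondary outcome at T1 and T2 in both arms. With 45% attrition expected by T1, however, T2 uptake will not be observed for all 640.

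It also stands that effectiveness is judged on the Decisional Conflict Scale alone, so neither the sample size nor the success criterion depends on the Glasgow Profile.

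**Conclusion.** The point holds for one secondary outcome. As written, the plan tests hearing-aid benefit between subsets formed by a choice made after randomisation, which the interventions are meant to influence. That comparison cannot be read as an effect of HearChoice at any sample size. This conclusion follows from the article's own text and needs no assumed figure.

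The second limb, low information, does depend on assumptions: uptake of 3% to 20%, 352 responders at T2 and equal arms. Within that range power for a difference of 0.3 is about 7% to 24%. The article does not establish that uptake will differ by arm, nor that bias will occur or in which direction. It establishes only that the design gives no protection against it.

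**What to change.** 1. In Statistical methods, exempt the Glasgow Profile from the between-group t-tests and from the analysis of variance of change. Report it descriptively by arm among adopters, with the number of adopters in each arm, and label it non-randomised.
2. Use the already planned *Action taken* outcome for the randomised comparison: hearing-aid uptake at T2 by randomised arm, as a risk difference with 95% CI, with all participants analysed in the arm to which they were allocated.
3. State how missing T2 responses are handled in that comparison, with a sensitivity analysis over plausible uptake among non-responders.
4. Confirm that the *Action taken* item separates taking up hearing aids from a step towards them, such as contacting a professional. The article does not show the item's wording. The survey needs some such distinction anyway to route the Glasgow Profile.

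The cost is wording in the protocol and the analysis plan, which the article says is still to be finalised. If the item makes the distinction in step 4, no new data are needed. The downside is that there will be no formal test of hearing-aid benefit between arms.

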**Ethics and dissemination:**

The study was approved by the Curtin University Human Ethics Committee (HRE2023-0024). All participants will provide written informed consent prior to participation. A broad dissemination plan of the study findings includes peer-reviewed publications, scientific conference presentations, articles and presentations for the wider community and public written in lay and accessible language, and social media.

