### Outcomes

Delivery of primary and secondary outcomes via an online survey is shown in table 1. Participants will be allowed to complete the survey up to 7 days following its delivery at T0, and 10 days for T1, 1m and T2. All questions, if applicable, are mandatory to enable progression through the survey. Reminders will be sent to facilitate survey completion: for T0, one reminder 2 days following initial survey delivery, and for T1 and T2, reminders at 2 days and 7 days following initial surveys.

**Table 1 T1:** Summary of outcomes, instruments and timepoint for administration at baseline (T0), 7 days post-intervention (T1) and 3 months post-intervention (T2)

Outcome	Instrument	Baseline (T0)	7 days (T1)	3 months (T2)

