	**Feasibility and implementation**			
Acceptability	Acceptability, usability, usefulness, satisfaction, accessibility		X	X
Consent rate	Completion at T0 vs number of those eligible	X		
Attrition	Completion at T1 vs T0	X	X	
Adoption	Uptake of intervention (treatment and control)	X	X	X
Fidelity (adherence)	Website analytics (throughout study)	X	X	X

To ensure high quality data, participants will be asked to complete an attention check at all time points prior to the outcome measures. The attention check is to identify whether participants can read and respond correctly to a simple instruction to minimise compromising data quality. Participants will be asked to indicate that they have read ‘Moderately interested’ and ‘Slightly interested’ in a sentence. Participants who fail the check at T0 will be excluded from the trial. Participants who fail at the other time points will be able to continue with the survey, but their failure of the attention check will be noted and potential impacts will be evaluated in the analysis.

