## Ethics and dissemination

### Ethics

The research study has been approved by the Curtin University Human Ethics Committee HRE2023-0024. Following presentation of the online Participant Information Sheet, informed consent will be indicated online by agreeing to a series of five statements to ensure the participant has understood the project (online supplemental appendix 2). Any protocol amendments to the protocol will be submitted to the Curtin HREC for approval, and the ANZCTR clinical trial registration will be updated. Anonymised data will be made available on completion of publication of the full programme of research on signing a unilateral data sharing agreement and will be made available for 5 years.

Financial and other competing interests for the principal investigators for the trial will be documented as required.

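### The outcome named consent rate is defined as T0 completion among eligible people, so it can only understate consent

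*Protocol article*

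**What the plan says.** The Secondary outcomes section defines consent rate as "completion of outcomes at T0 compared with those who are eligible", expressed as a percentage. The Feasibility and implementation block of Table 1 agrees: "Completion at T0 vs number of those eligible".

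Consent is described elsewhere as its own step. Under Ethics, after the information sheet, "informed consent will be indicated online by agreeing to a series of five statements". The abstract places it first: "All participants will provide written informed consent prior to participation".

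Two things stand between consent and completed T0 outcomes:

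- **Attention check.** The text after Table 1 says that "participants will be asked to complete an attention check at all time points prior to the outcome measures", and that "Participants who fail the check at T0 will be excluded from the trial".
- **Baseline survey.** The Outcomes section makes all applicable questions mandatory for moving on, plans one T0 reminder, and sets a response window: "Participants will be allowed to complete the survey up to 7 days following its delivery at T0".

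The Eligibility criteria section lists five inclusion criteria and one exclusion (current hearing aid use). The attention check is not among them. Attrition is defined as T1 completion relative to T0.

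**The concern.** The name and the formula describe different quantities. A consent rate tells a future trialist what share of suitable people are willing to join. The formula gives the share who were willing, got past the attention check and finished the baseline survey.

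Assessing feasibility is a stated objective. The article says these data are collected because no feasibility study came first, and that the results should inform later decision-aid trials. Reluctance to join, failing a screening question and abandoning a survey call for different remedies. A single percentage that merges them under a label naming only the first could point a later team to the wrong one.

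**Working it through.** **Plan's own figure.** The article gives no expected or target consent rate, so there is none to reproduce. The sample size does reproduce, 352 / (1 − 0.45) = 640, but consent does not enter it.

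**Formula.** Among eligible people, let
- *c* = share who agree to the consent statements,
- *f* = share of consenters who fail the T0 attention check,
- *b* = share of the remainder who stop before finishing T0.

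The rate as defined is *R* = *c*(1 − *f*)(1 − *b*). The true consent rate is *c*. So *R* never exceeds *c*, and equals it only if *f* = *b* = 0 (for *c* above zero).

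**Alternative denominator.** If those who fail the check were also removed from the eligible count, which the article does not say, the rate is *R′* = *c*(1 − *f*)(1 − *b*) / (1 − *cf*). Since *c* is at most 1, (1 − *f*)/(1 − *cf*) is at most 1, so *R′* cannot exceed *c* either.

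**Illustration.** The article gives none of *c*, *f* or *b*; all three are assumed here, with *c* = 80%.

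| *f* | *b* | *R* | Shortfall (points) | *R′* | Shortfall (points) |
|---|---|---|---|---|---|
| 2% | 5% | 0.80 × 0.98 × 0.95 = 74.5% | 5.5 | 0.7448 / 0.984 = 75.7% | 4.3 |
| 5% | 10% | 0.80 × 0.95 × 0.90 = 68.4% | 11.6 | 0.684 / 0.96 = 71.3% | 8.7 |
| 10% | 20% | 0.80 × 0.90 × 0.80 = 57.6% | 22.4 | 0.576 / 0.92 = 62.6% | 17.4 |

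With small losses the gap is small: *f* = *b* = 1% gives 0.80 × 0.99 × 0.99 = 78.4%, a shortfall of 1.6 points.

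**Break-off alone.** With *f* = 0 and *b* = 5%, 10% or 20%, *R* is 76%, 72% or 64%. This part does not depend on how attention-check failures are classified.

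**Is the loss captured by another named outcome?** Attrition starts from T0 completion, so it does not see these people. Adoption concerns uptake of the intervention, and fidelity concerns time spent on it. Neither counts consenters who failed the check or did not finish T0.

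**The case against.** The strongest reply is that the definition is open and consistent. Both places give the same numerator and denominator, and the percentage will be correct for that definition. This stands, and it limits the fault to a wrong name, with a downward bias for anyone who reads the figure as consent.

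The attention-check part is conditional. The article excludes those who fail from the trial but does not say whether they remain in the eligible count. Their absence from the eligibility criteria suggests that they do, without settling it. The break-off part holds either way.

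Some stronger readings are tempting but not supported:

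- *The losses will be reported nowhere.* The Statistical methods section promises a flow diagram based on Figure 1, which was not available in the text reviewed. Its list of counts is given only as examples. The diagram may show consent, and CONSORT reporting is also promised. What can be said is that no other named outcome measure separates the losses.
- *Non-completers will be treated as refusals.* Nothing in the article classes them so. A reader might draw that inference from the label.
- *The baseline survey is spread over a week.* The 7 days are a response window after delivery. Break-off is possible, but the text does not describe a battery taken in instalments.
- *The loss around randomisation is hidden.* Allocation happens on entry at T0 and is stored by the platform, so the number randomised can be set against T0 completion by arm.

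Finally, the order of eligibility screening and consent is not stated. If screening follows consent, dividing consenters by eligible people would give close to 100% by construction, so the fix must allow for that.

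**Conclusion.** The point holds as one of definition. The outcome called consent rate is T0 completion among eligible people, and as a measure of consent it can only be too low. The direction follows from the article's own wording. The size does not: in the assumed cases above, the shortfall runs from 1.6 points (1% lost at each step) to 22.4 points (10% failing the check and 20% of the rest breaking off), and it is smaller if failures leave the denominator.

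The importance is minor. The measure is descriptive, has no target or progression threshold, and does not touch the primary outcome, the sample size or the type I error. It is still worth correcting, because feasibility is a stated objective and the correction is cheap.

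**What to change.** 1. In the Secondary outcomes section and Table 1, define consent rate as the number agreeing to all five consent statements divided by the number eligible and invited to consent. If eligibility is screened only after consent, use the number shown the information sheet as the denominator.
2. Keep the present ratio, but call it T0 completion among eligible.
3. Report two further figures: T0 attention-check failures divided by consenters, and T0 completers divided by consenters. State whether those who fail the check stay in the eligible count.

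The cost is a change of wording and two extra descriptive counts. The online platform should already hold the underlying steps (an assumption to confirm with the platform team), so participants would have nothing more to do.

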#### Active control Group: Option Grid

A Hearing Loss Option Grid (a one-page PDF) that met IPDAS guidelines^36^ was developed for the Australian hearing healthcare system, based on an existing Option Grid developed in the UK (online supplemental appendix 1). The Option Grid was designed to provide a framework for decision-making about technology-based hearing management options, presented using written text. The option grid included three options (hearing aids, assistive listening devices and do nothing), and information for each option about what this involves, expectations, benefits, cost and extra considerations such as maintenance.

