#### Strategies to improve adherence to interventions

Participants can access their allocated intervention throughout the 3-month period of the trial by either bookmarking (*HearChoice*) or downloading (Option Grid) the intervention. Clear information will be presented to explain how this can be achieved. The 7-day period between allocation of the intervention (T0) and the primary endpoint (T1) will allow participants time to work through the content at their own pace and spend as little or as long as they choose. At T1 and T2 timeframes, the intervention will be offered again within the survey, with the option to bookmark or save. Similarly, the intervention will be re-presented at the 1-month timepoint in an email sent to nudge the participant that also asks them to think about their options, what actions they have taken and what actions they intend to take.

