### Data collection, management and analysis

#### Data collection and management

All data collected by BIT will be stored on BIT’s Google Drive compliant with ISO 27001,^46^ as well as the secure, password-protected Predictiv platform that only project team members can access. Personal email data collected at T1 to enable contact for the 1-month timepoint will be deleted at the end of the trial period. Data will be cleaned for test responses, duplicate hashed IP addresses (that limit the risk of individual identification), participant IDs and other unique identifiers related to the participant’s device. The cleaning code will be quality-assured by an independent researcher at BIT. Data will be sent securely to researchers at Curtin University and stored within a secure data storage drive based at Curtin University, Perth, Australia. This secure location is designed for storage of sensitive information and is the default storage option for research data generated at Curtin University. Data will be retained for a minimum of 7 years. A data management plan has been developed and approved by all partners involved in the RCT to detail data management procedures.

An attrition rate of approximately 45% between T0 and T1 is anticipated based on similar online studies.^47 48^ To promote participant retention and completion at T1, the duration from T0 to T1 is set at 7 days to give participants time to use the interventions in a timely manner and consider their hearing health needs and decision-making for the available options. We considered this time period sufficiently long to observe the intervention’s effects yet short enough to avoid significant participant attrition. The 1-month reminder email will be delivered as a behavioural ‘nudge’ in terms of intention and action to uptake hearing health. The allocated interventions will be made available to the participants throughout the trial. Interventions can be downloaded or bookmarked, and device-specific instructions will be provided to facilitate this. Additionally, the allocated intervention will be re-presented at T1, 1m and T2.

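### Fidelity in seconds from website analytics is not comparable between a web app and a downloadable one-page PDF, and probably under-records control use (minor)

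*Protocol article*

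**What the plan says.** The protocol article, under Secondary outcomes, defines fidelity as "time spent adhering to the allocated intervention across the study (s", with seconds as the unit. The definition refers to whichever intervention was allocated, so it covers both arms. Table 1 gives the instrument as "Website analytics (throughout study" and names no other source. Adoption is a separate row, described as "Uptake of intervention (treatment and control", with no instrument named. Both rows sit under the feasibility and implementation heading.

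The two interventions differ in form. HearChoice is a web-based app with six sections, reached by a link with a unique identifier. The control is "A Hearing Loss Option Grid (a one-page PDF". Under Strategies to improve adherence to interventions, repeat access is by bookmark for HearChoice and by "downloading (Option Grid) the intervention" for the control.

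Under Data collection and management, "the allocated intervention will be re-presented at T1, 1m and T2".

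Under Statistical methods, "Acceptability and feasibility data will be summarised by descriptive statistics and compared within and between intervention groups". That section also plans to explore whether engagement with the intervention affects outcomes over time between groups, and adds a website-analytics analysis of content viewed, for the HearChoice group only.

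**The concern.** One metric from one source is set for two products that leave different traces. A bookmark takes the user back to the site, where the visit can be logged. A downloaded PDF can be reread with no contact with any server. Ordinary use of the facility that the trial offers therefore moves some control reading outside the only named source, while most HearChoice use stays inside it.

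Two stated analyses would carry this. The first is the between-group comparison of feasibility data, in which the control could appear less used than it was. The second is the exploration of engagement as a factor in outcomes. If engagement is taken as analytics seconds, its measurement error depends on arm, so a difference between arms in the engagement-outcome relation could be an artefact of recording. Reading time that was never collected cannot be recovered at the analysis stage, so the remedy has to be in place while surveys are still being fielded.

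**Working it through.** **Plan's own figures.** The article gives no expected value for fidelity or adoption, so there is none to reproduce. Its only computed figures are those for sample size, and they can be confirmed as sound and separate from this point. With effect size 0.3, two-sided alpha 0.05 and 80% power, the t-test solution is 175.4 per arm, rounded up to 176, or 352 in total. With 45% attrition, 352 / (1 − 0.45) = 352 / 0.55 = 640. Fidelity enters neither calculation.

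**Passages side by side.**

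| Element | HearChoice | Option Grid |
|---|---|---|
| Form | Web app, six sections | One-page PDF |
| Return access | Bookmark | Download |
| Named source for fidelity | Website analytics | Website analytics |
| Offline use possible | My Plan page can be saved or printed | Whole document, once saved |
| Re-presented by the trial | T1, 1 month, T2 | T1, 1 month, T2 |

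The third and fourth rows conflict for the control: the whole product can leave the place where it is measured. For HearChoice only one output page can.

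**Direction and size.** Let f be the share of control use that is offline and unrecorded, and g the same share for HearChoice. Recorded time is (1 − f) of true time in the control and (1 − g) in HearChoice. The recorded HearChoice-to-control ratio is then the true ratio multiplied by (1 − g) / (1 − f). The documents give neither share, so all values below are assumptions.

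- With g = 0 the factor is 1 / (1 − f):
  - f = 0.25: 1 / 0.75 = 1.33
  - f = 0.50: 1 / 0.50 = 2
  - f = 0.75: 1 / 0.25 = 4
- With g = 0.25, to allow for saved or printed My Plan pages:
  - f = 0.25: 0.75 / 0.75 = 1
  - f = 0.50: 0.75 / 0.50 = 1.5
  - f = 0.75: 0.75 / 0.25 = 3

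The ratio is overstated whenever f exceeds g. That is likely, because all of the control can be read offline and only part of HearChoice can, but it is an inference. The factor multiplies whatever the true ratio is. The true ratio need not be near 1, since a six-section app with videos and a hearing test takes longer to work through than one page.

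**Counting period.** Fidelity is totalled over the whole study, during which the trial re-presents the intervention three times after T0. The article states no rule for including or excluding exposure from those prompts. For an engagement analysis of the T1 outcome, use after the T1 survey cannot have contributed to that outcome.

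**The case against.** The best counter-argument is that the only analysis naming website analytics is confined to HearChoice and based on content viewed, which PDF downloads cannot distort. On this view the between-arm contrast in seconds is read into a general sentence on feasibility data, and recording of control use is detail left to the full protocol or analysis plan. This stands in part. The contrast is an inference, but Table 1 places fidelity among the feasibility measures, the definition covers both arms, and the HearChoice-only work is introduced as additional. Outcome, unit, instrument and comparison are all fixed in the article itself.

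It is also fair that downloading is optional, that the control is offered again inside the surveys where viewing might be logged, and that My Plan can be saved or printed. These points reduce the size of the problem but do not make the seconds comparable.

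A reader might infer more than the text supports:

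- **That re-presentations are counted as use.** No counting rule is given. The schedule is the same in both arms, so this is not in itself a between-arm bias.
- **That adoption is distorted in the same way.** Analytics is named for fidelity only. Whether a link was opened or a file downloaded can be recorded for a PDF, and later rereading does not change it.
- **That the result for the third objective is biased.** That objective concerns the acceptability and feasibility of HearChoice itself, not a contrast in engagement with the control.

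**Conclusion.** The point holds in a limited form. Seconds from website analytics are not comparable between a web app and a downloadable PDF, and a between-arm contrast would probably under-record control use. Any engagement analysis built on those seconds would inherit the problem. The amount is unknown. The factors of 1.33 to 4 rest wholly on assumed offline shares of 25% to 75% and are illustrations, not estimates. The direction rests on two assumptions: that reading a saved file leaves no website record, and that a larger share of use is offline in the control than in HearChoice.

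Severity is minor. Fidelity is a descriptive feasibility measure and, at most, an exploratory explanatory variable. The primary outcome, the success criterion, the sample size and the HearChoice-only content analysis are untouched. The handling of prompted use is a secondary point: the whole-study period does not exclude it, so absolute use in either arm may partly reflect the trial's own prompts.

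**What to change.** 1. Report analytics time and content viewed for HearChoice only, and state that seconds will not be compared between arms.
2. For between-arm fidelity and for the engagement analysis, use a measure available in both arms: whether the link was opened or the file downloaded, plus one self-report item on use of the allocated intervention, worded identically in both arms at T1 and T2.
3. As a secondary change, report use between the T0 offer and the opening of the T1 survey separately from sessions opened through the T1, 1-month and T2 re-presentations.

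The cost is one item in each of two existing surveys and a few lines in the analysis plan. The downside is recall error. It may differ somewhat between arms, because remembering several visits to an app is not the same task as remembering one page, so the self-report result should be presented as approximate, beside the opened-or-downloaded record.
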